**Discussion:**

The design of this pilot study may support the adoption of library-facilitated telehealth treatment as a feasible and acceptable strategy to engage and retain people experiencing homelessness with OUD in buprenorphine treatment.

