#### Feasibility of RCT to evaluate the current intervention

Rate of enrollment (Number of participants per week and per month).Proportion of interested and eligible participants who can successfully complete enrollment in the study.Study retention (proportion of RCT-enrolled participants who complete each follow-up assessment).Proportion of RCT-enrolled participants for whom outcome data are collected.We will track the proportion of participants who indicate willingness to be assigned to either condition (the percent of people who decline to participate because they do not like the randomization aspect of the study should be “none” to determine whether the study is feasible).

As a pilot study that is not statistically powered to assess efficacy, the study will provide effect size estimates of the library-facilitated telehealth BBB intervention on the primary outcomes, buprenorphine uptake and adherence, as measured by (1) presence of buprenorphine in weekly urine drug screenings at the library and at FJV health center, (2) buprenorphine prescription pick-ups, and (3) number and frequency of clinic visits, with secondary outcomes including use of fentanyl (e.g., illicitly manufactured) and other opioids (secondary outcome measured in weekly urine drug screens), and (4) self-reported substance use, mental health, and quality of life measures at 1-,2-,4-,8-, and 12-weeks, compared to a control group.

The control group will undergo the same procedures and receive the same incentives from the study staff in the library in terms of weekly assessments. They will also receive the same care from the clinic, except they will not be instructed to use the library telehealth option for their medical visits like the treatment group until their study participation is over. We hypothesize that patrons assigned to the library-facilitated telehealth group will uptake buprenorphine, pick up their buprenorphine prescriptions from the pharmacies, take buprenorphine after two weeks, and adhere to medical appointments more than the control (in-person clinic visits) group.

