Unstably housed individuals who express an interest in obtaining buprenorphine to treat their current opioid use are invited to a reserved public library room for screening. In-person screenings are then conducted by research staff using a computer-assisted questionnaire to assess eligibility. The researchers obtain written informed consent from the participants to access their FJV Health Center medical record data about their medical appointment adherence for opioid use disorder and drug screenings on-site. Participants also consent to researchers searching CURES (Controlled Substance Utilization Review and Evaluation System), a state-level database of dispensed controlled substance prescriptions, allowing researchers to confirm whether participants picked up their controlled medications from the pharmacy. Participants indicate their preferred language for communication (English or Spanish). Researchers fluent in the selected language then review the corresponding consent form, also in their preferred language, with the participants.

For both the library-facilitated telehealth and control arms of the study, study enrollment is initiated by the study staff; enrollment is completed when the participant attends their first medical buprenorphine appointment in-person at the FJV Health Center and a medical provider confirms their eligibility for buprenorphine. Participants travel by foot from the downtown library (10-minute walk) or by trolley/bus from the Mission Valley Library to FJV Health Center. Participants receive transportation passes throughout the study. FJV prefers patrons attend the first clinic visit in-person for closer screening of buprenorphine eligibility. The study will track the number of patrons who initiate enrollment but do not make it to FJV to complete their enrollment.

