### Outcome ascertainment and post-intervention assessments

Intervention outcomes determine the feasibility, acceptability, and retention in the library telehealth intervention at baseline, 1-,2-,4-,8-, and 12-weeks on (1) weekly urine drug screenings (for buprenorphine uptake and other drugs); (2) buprenorphine prescription pick-ups; (3) clinic visits; and (4) self-reported measures (e.g., substance use, mental health, quality of life). (see Table 1).

**Table 1 Tab1:** BBB intervention targets, strategies, and specific activities

**Intervention targets**	**Intervention strategies**	**Examples of specific activities**	**Data Collection Format**
Feasibility and acceptability of library telehealth for buprenorphine uptake (pharmacy pickup, taking prescription one or more times) and adherence (more than one buprenorphine positive screen or taking buprenorphine for 8 + weeks)	Participants use library telehealth. Data are used to assess participant satisfaction (in exit interviews) and identify areas for improvement.	All participants in the library-facilitated telehealth and control groups complete a post-treatment satisfaction survey regardless of whether they sustained in treatment. At the end of the participants’ 12-week participation in the study, research staff interview participants about their experience with library telehealth and the acceptability of BBB study participation. The investigators survey medical providers and library staff involved in the study about their experiences with the study protocol.	Surveys and interviews, delivered by a researcher not involved in their care. Satisfaction measures are embedded in the follow up exit survey and interview using specific items generated by the study about the telehealth and study experiences.
Awareness of buprenorphine availability	Basic buprenorphine education, increase in knowledge of service providers.	General information on buprenorphine availability at Father Joe’s Villages and in the San Diego region.	Personalized discussion, resource list delivered by researchers and library social work interns.
Apprehension toward buprenorphine*	Basic buprenorphine education, increase knowledge of health.	General background on buprenorphine treatment (e.g., targeting of opioids). Facts about buprenorphine. Buprenorphine treatment information.	Brief educational information sheets delivered by researchers/library social work interns and FJV Health Center staff.

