**Primary Outcomes**		
Buprenorphine uptake and adherence	Biomarkers: urinary drug assessments at the library and clinic. Pharmacy pickups of buprenorphine Self report: “How often do you take it? What is the dosage? Are you taking it correctly (as prescribed)? If not, why?” “Did you run out of your prescription before getting a refill?” “Have you stopped taking buprenorphine?”	Study generated Uptake: the proportion of people who pick up from the pharmacy and take buprenorphine 1 or more times at initiation, i.e., during the first 2 weeks, confirmed by biomarkers (urinary drug screens at the library and clinic, pharmacy pickup data from the state’s CURES database) Adherence = more than one buprenorphine positive screen taken at the library or at the FJV Health Center, ideally for 8 + weeks.

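### The trial hypothesises buprenorphine use beyond two weeks and looks towards treatment retention, but no defined outcome requires evidence of buprenorphine after week 2

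*Protocol article*

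**What the plan says.** Under *Feasibility of RCT to evaluate the current intervention*, the Protocol article expects telehealth participants to start buprenorphine, collect it, and "take buprenorphine after two weeks, and adhere to medical appointments more than the control (in-person clinic visits) group". The abstract's Discussion hopes to support "a feasible and acceptable strategy to engage and retain people experiencing homelessness with OUD in buprenorphine treatment". *Outcome ascertainment and post-intervention assessments* adds: "Intervention outcomes determine the feasibility, acceptability, and retention in the library telehealth intervention at baseline, 1-,2-,4-,8-, and 12-weeks".

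The outcomes are defined as follows.

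- **Uptake.** Table 2 counts people who pick up and "take buprenorphine 1 or more times at initiation, i.e., during the first 2 weeks". *Baseline and longitudinal assessments/measures* uses the same two-week window. The Methods text that follows the hypothesis allows a pick-up and one dose at any time in the study period.
- **Adherence.** Table 2 and the Methods text require more than one positive screen, at the library or the clinic, with eight or more weeks as an ideal. The same Methods text later says one or more positive tests. Table 1 joins the screen rule and the eight weeks with *or*. *Sample size and planned data analyses* says taking the drug more than once.
- **Appointment adherence.** Two or more attended visits, with no timing.
- **Retention.** The one defined measure is "Study retention (proportion of RCT-enrolled participants who complete each follow-up assessment"), listed as a metric of trial feasibility.

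**The concern.** Randomisation follows the in-person intake visit and the provider's confirmation of eligibility (*Randomization and intake*). After that, the arms differ only in whether library video follow-up is offered (*Control condition*). The intervention can therefore act only after intake, mainly on whether people stay in treatment. That is what the hypothesis and the abstract's closing claim address, and it is where no firm outcome exists.

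Two things are at stake. First, the hypothesis about use beyond two weeks has no outcome matched to it, and a statement about treatment retention would have no defined estimate behind it. Second, *Sample size and planned data analyses* says the adherence estimates will be the basis for power calculations in future efficacy trials. A proportion that can be reached within two weeks is a poor planning figure for a trial of continued treatment.

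**Working it through.** The article gives no figure on this point to reproduce. The check compares definitions, followed by an illustration.

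**Step 1: can each outcome be met without buprenorphine after week 2?**

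| Outcome | Minimum evidence | Evidence after week 2 required? |
|---|---|---|
| Uptake (Table 2) | pick-up and one dose in weeks 1–2 | No |
| Uptake (Methods text) | pick-up and one dose at any time | No |
| Adherence (Table 2, Methods text) | two positive screens | No; screens are weekly, so weeks 1 and 2 suffice |
| Adherence (later Methods wording) | one positive test | No |
| Adherence (analysis section) | taken more than once | No |
| Adherence (Table 1) | two positive screens, or eight or more weeks | No; the first branch suffices |
| Appointment adherence | two attended visits | No timing, and not a measure of drug use |
| Study retention | completed assessments | Not a measure of drug use |

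A participant who takes buprenorphine for 14 days, gives positive screens in weeks 1 and 2 and then stops is scored as uptake yes and adherence yes.

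**Step 2: how far can adherence and continued treatment differ?** The documents give no stopping rate, so one is assumed and varied. Let h be a constant weekly probability of stopping. Everyone starts, every weekly screen is attended, and a screen is positive exactly while the person is on treatment. Then:

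- adherent (two or more positives) = (1 − h)²
- on treatment at week 3 = (1 − h)³
- on treatment for eight or more weeks = (1 − h)⁸
- on treatment at week 12 = (1 − h)¹²

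| h (assumed) | Adherent | Week 3 | 8+ weeks | Week 12 |
|---|---|---|---|---|
| 5% | 0.95² = 90% | 86% | 66% | 54% |
| 10% | 0.90² = 81% | 73% | 43% | 28% |
| 20% | 0.80² = 64% | 51% | 17% | 7% |

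**Step 3: what would an arm comparison show?** Read two rows of the table as two arms, again purely as an illustration.

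- 5% against 10%: adherence differs by 90 − 81 = 9 points, eight or more weeks by 66 − 43 = 23, week 12 by 54 − 28 = 26.
- 10% against 20%: the differences are 81 − 64 = 17, 43 − 17 = 26 and 28 − 7 = 21.

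In both pairs the adherence outcome shows a smaller difference than either later measure. The exact gap depends on the assumed rates.

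**Step 4: are data available to do better?** Yes. Participants consent to searches of the state dispensing database (CURES), "allowing researchers to confirm whether participants picked up their controlled medications from the pharmacy". Clinic urine screens are routine in both arms, clinic attendance and clinic screen results are recorded (*Data tracking and management*), and Table 2 includes a question on having stopped. The library screens and the survey item are seen only if the participant attends. The dispensing and clinic records do not depend on library attendance.

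**The case against.** The strongest reply is that the article collects ample information on continuation and leaves its derivation to a fuller document. That is right about the data, and it rules out several stronger readings that a reader might infer:

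- *That only attendance at paid study visits is measured.* It is not. Pick-ups, clinic screens and clinic appointments are captured apart from library visits, and participants are asked whether they have stopped.
- *That pharmacy records serve only to confirm uptake.* The paragraph before the hypothesis lists pick-ups among the measures of uptake and adherence together. They are simply absent from the adherence definition itself, which rests on screens.
- *That stopping treatment and leaving the study are confused.* Study retention is labelled as such and placed under trial feasibility, and the limitations section discusses treatment retention separately, with caution.
- *That someone who leaves the library visits but stays in treatment must score as non-adherent.* Clinic screens are required in both arms and count towards adherence.

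Nor do the documents support a figure for how far misclassification would dilute the arm difference, because they give no misclassification rates.

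It is also fair that this is a pilot whose objective is feasibility and acceptability, not powered for efficacy, and that the abstract says only that the design may support adoption. With an assumed 20 per arm and a 50% rate in each, the 95% half-width for a difference is 1.96 × √(2 × 0.5 × 0.5 / 20) = 31 points, so any arm contrast will be imprecise.

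What does not stand is the appeal to a fuller document. The article itself fixes both the hypothesis and the outcome definitions, and they do not match. Being a pilot does not remove the need, since the estimates are meant to inform the next trial's power.

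**Conclusion.** The concern holds as a mismatch between hypothesis and outcomes. The trial hypothesises use beyond two weeks and looks towards treatment retention, yet every firm outcome can be met without evidence of buprenorphine after week 2, and the eight-week element is not binding. The data needed to date discontinuation are collected; what is missing is an outcome defined from them.

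The definitional result needs no assumption beyond the stated weekly screening. Its size does. Under constant weekly stopping of 5% to 20% with full screen attendance, adherence would read 90% to 64% while 54% to 7% remain on treatment at week 12. Those rates illustrate direction and possible scale and are not a forecast. The change should be made because it is cheap and lets the pilot estimate the quantity it is about; the trial's feasibility aims are unaffected.

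**What to change.** In Table 2 and *Sample size and planned data analyses*:

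1. Add one treatment-retention outcome for every randomised participant, whether or not they still attend the library. An example is a CURES buprenorphine pick-up in a pre-set late window such as weeks 9–12 from randomisation (yes/no), with the date of the last pick-up as supporting information on time of stopping. Check the window against the usual length of supply, which the article does not give, so that a person still covered by an earlier pick-up is not counted as having left treatment.
2. Map the hypothesis on use after two weeks to a dated outcome: a pick-up or positive screen after week 2.
3. State one adherence threshold and use it throughout.
4. Report these outcomes separately from study retention. Base statements about treatment retention, and the inputs to future power calculations, on them.

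The cost is wording in two places and a CURES look-up after week 12 under consent already obtained. One small downside is that a pick-up does not prove the drug was taken, so library and clinic screens should stay as supporting evidence.

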**Methods:**

The study is a partnership between the San Diego Public Library and a federally qualified healthcare center attached to a homeless shelter (Father Joe’s Villages (FJV) Village Health Center). We co-designed a pilot randomized controlled trial to assess the feasibility and acceptability of a library-facilitated telehealth intervention in San Diego, California. The intervention is being evaluated for its feasibility and acceptability (library tele-buprenorphine uptake) by obtaining an estimate of the effect of the library telehealth arm of the intervention on buprenorphine treatment outcomes (primary outcome: buprenorphine uptake, i.e., a pharmacy pickup and taking the prescription 1 + times) and adherence (i.e., > 1 buprenorphine positive screens, ideally for 8 + weeks), compared to the control (standard care at the clinic) intervention. Individuals reporting homelessness and OUD (with or without other substance use) are eligible. Forty library patrons will be recruited via flyers, screened for eligibility, and referred to FJV Health Center for in-person initial buprenorphine treatment intake visits. Participants who complete intake are enrolled and randomized to the library-facilitated telehealth condition, which involves using library internet and computer resources for follow-up buprenorphine treatment appointments with the medical provider via library telehealth. In the control condition, participants do not use library telehealth for their buprenorphine care follow up appointments, but rather they go in-person to the clinic or per usual standard care protocols. Feasibility and acceptability of the library telehealth intervention and conduct of the randomized controlled trial are determined by the participants’ use of the library telehealth intervention for buprenorphine treatment, and quantitative and qualitative measures assessing their perceptions of the library telehealth intervention, collected over a 12-week period.

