As a primary outcome, buprenorphine *uptake* is defined as a pharmacy pickup and taking the prescription one or more times during the study period. Buprenorphine *adherence* is indicated by more than one buprenorphine positive screens taken at the library or at FJV Health Center and ideally continuing to take buprenorphine as prescribed for eight or more weeks. The rationale for the primary outcomes, buprenorphine uptake and adherence, via weekly drug screening, is to try to capture the patterns of buprenorphine uptake and adherence among unhoused populations, a likely more isolated and neglected group when it comes to finding, starting, and adhering to buprenorphine due to being unhoused. Therefore, we measure adherence as a primary outcome with 1 + buprenorphine positive tests, ideally for 8 + weeks of 12 weeks (3 months), rather than the standard 3–12 months adherence.

In the study’s formative stages of intervention development, study staff conducted interviews and focus groups with library patrons (those experiencing homelessness or living in a shelter or treatment program), library staff (i.e., security personnel, librarians, outreach workers), general public/parents, and buprenorphine providers to get reactions to the proposed program and to inform the study design. For example, five focus groups with library patrons were conducted across four libraries in San Diego to assess the potential feasibility and acceptability of the planned intervention. The findings from these interviews and focus groups inform the design of the telehealth intervention at the libraries and the measures that can be used in a randomized controlled trial. For example, we gained insights for recruiting and screening participants for opioids (being discreet in public spaces), enrollment procedures (coordinating with medical providers), and timing of the randomization (after first buprenorphine medical provider visit). Another recommendation made is to have persons with lived experience, especially with substance use recovery and experiences with buprenorphine, on the team. Focus group participants suggested recruitment strategies such as placing flyers at specific library bulletin boards frequently visited by unhoused individuals, which many identify as providing a consistent and reliable source of community information.

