### Data collection

#### Baseline and longitudinal assessments/measures

Following a FJV Health Center physician’s buprenorphine prescription, research staff track the participants’ buprenorphine medication uptake (pharmacy pickup, taking prescription one or more times during the first two weeks in the study), adherence (more than one buprenorphine positive screen), and medical appointment keeping through urinary drug screenings, interviews conducted at public libraries, and medical record data. All participants are invited to return to the library weekly for urinary drug screenings and to complete follow-up survey assessments at weeks 1, 2, 4, 8, and 12. Baseline and follow-up assessments are conducted in reserved library study rooms or conference rooms.

The 60-minute baseline survey captures the following domains: sociodemographic, behavioral, social supports, telehealth utilization and comfort, library usage, substance use behaviors, overdose experiences, and treatment history, along with the biomarker and medical record data collection (see Table 2). The content of the follow-up surveys is the same as the baseline surveys except that participant history and demographics are removed. The follow-up survey is shorter (30 min), retaining questions surrounding buprenorphine uptake, healthcare utilization, and barriers and facilitators to use. Follow-up questions also ask participants to recall experiences since their last visit with the research team in the library, particularly to determine the feasibility and acceptability of the library telehealth intervention; ease and understanding of being in the randomized controlled trial; experiences following up with the medical provider whether in-person or by telehealth; and their experiences with picking up and taking the buprenorphine medication.

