#### Sample size and planned data analyses

Our target sample size for the trial is 40 participants, although we allow for a maximum of 60 participants to account for attrition. The sample size will provide adequate precision for effect size estimates, though not statistically powered to assess efficacy on primary outcomes.

Buprenorphine uptake (the proportion who pick up and take buprenorphine at initiation, confirmed by CURES database pharmacy pickup records and urinary drug screenings) and adherence (taking buprenorphine > 1 time, ideally for 8 + weeks), medical appointment adherence (attended medical appointments for buprenorphine two or more times as confirmed by clinic medical record data) will be divided by the number prescribed and scheduled, respectively.

Adherence estimates from this study will also provide the basis for power calculations in the design of future efficacy trials. Quantitative data analysis will consist of univariate statistics to describe the entire study sample and by study arm, the prevalence of individual responses, and the prevalence of treatment uptake and adherence. We will conduct an intent-to-treat (i.e., per-randomization) analysis following CONSORT guidelines to explore potential differences between study arms on the outcomes. Specifically, we will use regression models testing each outcome separately (using the appropriate test depending on the outcome distribution, e.g., logistic regression with binary outcomes). These models will treat the intervention condition (library-facilitated telehealth intervention vs. treatment-as-usual control) as the exposure in unadjusted models.

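### Adherence, a named primary outcome, is worded in four ways that score some participants differently, and its commonest rule can be met within the first two weeks

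*Protocol article*

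**What the plan says.** The protocol article treats adherence as a primary outcome in its objectives and in Table 2. Its definitions are:

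- **More than one positive screen.** The Abstract has "adherence (i.e., > 1 buprenorphine positive screens, ideally for 8 + weeks", and the Background is in similar terms. The outcome paragraph in the objectives has "more than one buprenorphine positive screens taken at the library or at FJV Health Center and ideally continuing to take buprenorphine as prescribed"; the ideal duration given there is at least 8 weeks. Table 2 has "Adherence = more than one buprenorphine positive screen taken at the library or at the FJV Health Center, ideally for 8 + weeks". The data collection section gives the threshold with no duration: "adherence (more than one buprenorphine positive screen".
- **One or more positive tests.** The same outcome paragraph ends with "we measure adherence as a primary outcome with 1 + buprenorphine positive tests, ideally for 8 + weeks of 12 weeks (3 months".
- **More than one positive screen, or eight weeks of use.** Table 1 has "more than one buprenorphine positive screen or taking buprenorphine for 8 + weeks".
- **Taken more than once.** The section on sample size and planned analyses has "adherence (taking buprenorphine > 1 time, ideally for 8 + weeks", with no screen mentioned.

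That last section also says that the adherence estimates will be the basis for power calculations in future efficacy trials, and that each outcome will be compared between arms in its own regression model.

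**The concern.** A primary outcome needs a rule that turns one participant's data into one value. Here the threshold, the thing counted (screens or doses) and the role of the eight weeks all change from section to section. A qualifier such as ideally cannot be coded, and no section says which wording enters the regression. If this is left open, the rule could be chosen after the results are known, and the rate handed to the next trial's sample size would have no fixed meaning.

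The commonest rule also fits the stated aims poorly. The objectives hypothesise that telehealth participants will be taking buprenorphine after two weeks more often than controls, and say that weekly screening is there to capture patterns of use. More than one positive screen can be reached inside the first two weeks. Because library and clinic screens both count, it could even be reached inside one week.

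**Working it through.** **Step 1: do the wordings classify people differently?** Call the four rules A (two or more positive screens), B (one or more), C (two or more positive screens, or taking it for 8+ weeks) and D (taken more than once).

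| Participant | A | B | C | D |
|---|---|---|---|---|
| Several doses, one positive screen, later screens missed | no | yes | no | yes |
| Reports 8+ weeks of use, only one screen done, positive | no | yes | yes | yes |
| Reports two doses, no positive screen | no | no | no | yes |
| Positive in weeks 1 and 2, then never again | yes | yes | yes | yes |
| Positive in all 12 weeks | yes | yes | yes | yes |

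The first three rows show the inconsistency. The last two show that no rule separates brief from sustained use. Rule B also comes close to repeating uptake, which Table 2 confirms partly by urine screens in the first two weeks.

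**Step 2: how far apart are the two written screen thresholds?** The documents give no expected adherence or positivity, so there is no figure to reproduce and the inputs are assumptions. Take 12 weekly screens (weekly screening for 12 weeks, as in the article), mean weekly positivity m, and within-person correlation ρ in a beta-binomial model with a + b = 1/ρ − 1 and a = m(a + b).

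The gap between one or more and two or more is the probability of exactly one positive screen.

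- With m = 0.5 and ρ = 0.3: a + b = 2.333 and a = b = 1.167.
- P(0) = ∏ (b + j)/(a + b + j), j = 0 to 11, = 0.063.
- P(1) = P(0) × 12a/(b + 11) = 0.063 × 14.0/12.167 = 0.072.
- One or more: 1 − 0.063 = 93.7%. Two or more: 93.7 − 7.2 = 86.5%.

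Other settings:

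| Positivity | Correlation | 1 or more | 2 or more | Gap (points) |
|---|---|---|---|---|
| 30% | 0.3 | 79% | 64% | about 15 |
| 70% | 0.3 | 99% | 96% | about 3 |
| 50% | 0.5 | 83.9% | 75.5% | 8.4 |
| 10% | 0 (independent weeks) | 71.8% | 34.1% | 37.7 |

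**Step 3: does the low cut-off lose information?** Simulated power with 20 per arm (40 in total, 1:1 assumed), shown only to compare how much each summary retains:

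| Weekly positivity by arm | Correlation | 2 or more | 8 or more | Count of positive weeks |
|---|---|---|---|---|
| 40% vs 60% | 0.3 | 27% | 39% | 55% |
| 40% vs 60% | 0.5 | 27% | 28% | 39% |
| 20% vs 40% | 0.3 | 52% | 32% | 63% |

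The count does best in each row. Which cut-off is better depends on the assumed positivity.

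**Step 4: what if attendance differs by arm?** Suppose true positivity is 60% in both arms, and 80% of weeks are screened in one arm and 60% in the other. Counting missed weeks as not positive gives 12 × 0.60 × 0.80 = 5.76 weeks against 12 × 0.60 × 0.60 = 4.32, a spurious difference of 1.44 weeks. Among observed weeks both arms show 60%, provided that missing a screen is unrelated to use.

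**The case against.** One rule clearly dominates. More than one positive screen appears in the Abstract, Background, objectives, data collection section and Table 2. The one-or-more wording comes shortly after it in the same paragraph and may be shorthand, as may the analysis section's wording. The rules are partly nested, so calling them four incompatible definitions would be too strong. This stands as a limit on the size of the problem. It does not remove it, because the table and the analysis section still score some people differently.

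A reader might infer that the same data could give more than 90% or less than 40% adherent depending on the sentence followed. The documents do not support that. The low figure would need eight positive screens of twelve as a rule of its own, and no section sets one. Eight weeks is either only an ideal or, in Table 1, follows an or and so widens the definition.

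A reader might also infer that the low cut-off must sit at a ceiling and hide a retention effect, or that the weekly results will be thrown away. The first depends on positivity: at 20% vs 40% the low cut-off beats the high one. The second is not stated, since the regression is to suit the outcome's distribution and logistic regression is only an example.

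Finally, the article explains that it uses a lenient measure for a hard-to-reach population, and the pilot is declared not powered for efficacy. Preferring a count is therefore a recommendation, not the correction of an error. An analysis plan that is not shown may settle the rule, but that would not remove contradictions within this article.

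**Conclusion.** The inconsistency is real and should be corrected, because adherence is called primary and is meant to feed later power calculations. As written, following the article does not lead to a single adherence result. That conclusion rests on the wording alone.

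The numerical effect is uncertain. Between the two written screen thresholds it is about 7 points at 50% positivity and correlation 0.3, less when use is common and more when it is rare. The size of the shift under the Table 1 and analysis-section wordings cannot be derived from the documents.

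The weaker part concerns fit to purpose. The dominant rule can be satisfied in the first two weeks, so it does not capture the continued use that the trial hypothesises. A count of positive weeks would, and it retained the most information in each setting shown, under assumed inputs.

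**What to change.** Use one scorable definition, worded identically in the Abstract, Background, objectives, Table 1, data collection section, Table 2 and planned analyses. Delete the word ideally and Table 1's alternative of taking the drug for eight weeks.

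Preferably, define adherence as the number (or proportion) of study weeks 1 to 12 with a buprenorphine-positive library or clinic screen. Allow one result per week, and state which result is used when both sites have one. Compare arms with a 95% confidence interval. Report two or more and eight or more positive weeks as descriptive summaries only.

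Missed weeks need care. Telehealth visits take place in the library, where the weekly screens are done, so attendance may differ by arm. Report the number of weeks screened by arm, and give the result both with missed weeks counted as not positive and among observed weeks only. The first can turn an attendance difference into an adherence difference. The second assumes that missed weeks resemble observed ones.

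The cost is a change of wording and a little more analysis, with no new data. The headline figure will look less favourable than a rate based on more than one positive screen.
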